### Power calculations

A power calculation indicates that a sample of 600 participants would provide 80% power (at the 5% level) of detecting an increase of 11% in the TEL-SUPP and TEL-SUPP-AR groups versus no increase in the Control group and a 3% increase in the telephone reminder group (TEL), assuming a base attendance rate of around 69% (as currently present in vigintiles 1–12). This would also equate to 67% power (at 5% level) of detecting an increase in uptake of 9% spread across the 3 telephone intervention arms versus the Control group.

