### Sampling and randomisation

Participants will be selected from those receiving an appointment for breast screening who do not telephone to cancel their appointment and who fail to attend or to re-arrange their appointment before the reminder letter is due to be sent. Sampling will be from the lists of women for whom reminder letters are generated. Postcodes will be used to derive Scottish Index of Multiple Deprivation (SIMD) vigintiles, and women who are from a SIMD vigintile between 1 and 12 inclusive (where 1 represents the most deprived areas), for whom telephone numbers can be obtained, will be randomised to treatment arm in a 1:1:1:1 ratio.

In order to achieve a balance between treatment groups, randomisation will be carried out by a member of the research team who is independent of the intervention on a record by record basis using minimisation via the MINIM software program [20] with age band (50–56, 57–63, 64 or older) and SIMD quintiles (i.e. 1, 2, 3 equivalent to vigintiles 1–4, 5–8 and 9–12) as the minimisation variables. The minimisation algorithm allocates the first record randomly and subsequent participants are allocated to minimise the imbalance between groups on the minimisation variables. It is currently the best available method of achieving randomisation whilst “ensuring excellent balance between groups for several prognostic factors, even in small samples” [21]. To ensure that the researcher does not influence the randomisation process, participants will be entered into the MINIM software sequentially, according to their order in the reminder letter list and the researcher will also remain blind to the identity of each treatment group (i.e. by randomising only to A, B, C, or D) during the randomisation process. The same researcher will collect the three-month follow-up data and carry out the data analysis and will continue to remain blind to the identity of each treatment group until this is complete.

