### Analysis

Our primary analysis will be chi-square to detect differences in the proportion of respondents who attended breast screening within 3 months of the reminder letter or call as a function of the 4 arms (control, TEL, TEL-SUPP or TEL-SUPP-AR). This will be followed by logistic regression of attenders versus non-attenders in the four groups, controlling for potential between-arm differences in age, social deprivation (SIMD) and history of previous breast screening attendance. Our primary analysis will be on an ‘Analysed as Allocated’ basis, i.e. including all participants, whether or not they were successfully contacted by telephone and/or agreed to take part in the study. Secondary analysis will be conducted for those agreeing to and participating in the intervention (TEL-SUPP and TEL-SUPP-AR groups only) to test the mediating and moderating roles of reported barriers, intention and AR in uptake of screening after reminder.

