### Timetable

This is a 17-month project. Months 1–3 will be spent designing the telephone support intervention and developing the barriers checklist and recruitment procedures. During this period we shall obtain IT approval for the Research Fellow to access the required databases, as well as Caldicott approval for the data extraction. The Research Fellow will also gain an NHS Tayside ‘letter of access’, which permits access to the required data systems, for the duration of the study.

Months 4–9 will be spent conducting the telephone intervention. We plan a sample size for analysis of 600; with 450 women randomised to the three telephone interventions, this equates to around 75 telephone calls per month.

We require a three-month lag after the intervention to collect data on screening attendance. Therefore, months 10–15 will be spent collecting the data on screening attendance and analysing the data. The training materials will also be developed during this time. In months 16–17, we will produce a final report and a paper of the main results for publication, and hold presentations on the results for NHS Tayside staff.

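### The stated 80% power does not hold for the planned four-arm chi-square, which has about 63% at 600 women; the 67% figure also does not match a stated test

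*Protocol article*

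**What the plan says.** All references are to the protocol article.

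- **Primary test (Analysis).** "Our primary analysis will be chi-square to detect differences in the proportion of respondents who attended breast screening within 3 months". The comparison is across four named arms, kept separate, and includes every allocated woman whether or not she was reached by telephone.
- **80% power (Power calculations).** "a sample of 600 participants would provide 80% power (at the 5% level) of detecting an increase of 11" percentage points. That gain is assumed for both support arms; Control is taken to show none and the reminder-only arm 3 points. Control attendance is set at about 69%.
- **67% power (same section).** The same sample is said to give "67% power (at 5% level) of detecting an increase in uptake of 9% spread across the 3 telephone intervention arms versus the Control group".
- **Allocation.** Women "will be randomised to treatment arm in a 1:1:1:1 ratio" (Sampling and randomisation), and the Timetable plans 600 for analysis "with 450 women randomised to the three telephone interventions". That is 150 per arm.

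The power section does not name the test behind either figure, and it does not say whether the 5% level is one- or two-sided.

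**The concern.** A chi-square on a table of four arms by two outcomes has 3 degrees of freedom and no direction. It spreads its sensitivity over every pattern of difference between arms, so it needs a larger non-centrality than a single focused contrast to reach a given power. The article supplies every input needed to check the 80% figure against this test, and the figure is not reached.

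The sample size of 600 rests on this statement. If the planned test has 63% power, the chance of missing the assumed effect is 37%, not 20%. Someone judging the trial's size or interpreting a non-significant result would be working from the wrong figure.

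**Working it through.** **Inputs.** 150 women per arm (1:1:1:1 of 600; 450 in the telephone arms). Level 5%. Control 69%. Increases read as absolute percentage points. First scenario: 69/72/80/80%. Second scenario, if each telephone arm gains 9 points: 69/78/78/78%. No dropout, because all allocated women are analysed.

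**Planned test.** The non-centrality is λ = n Σ(pᵢ − p̄)² / [p̄(1 − p̄)] with n = 150. Power is the probability that a non-central chi-square with 3 df exceeds 7.815.

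*First scenario*
- p̄ = (0.69 + 0.72 + 0.80 + 0.80)/4 = 0.7525
- Σ(pᵢ − p̄)² = 0.003906 + 0.001056 + 0.002256 + 0.002256 = 0.009475
- λ = 150 × 0.009475 / (0.7525 × 0.2475) = 7.63
- Power = 63.1% (simulation 63.2%), against 80% stated
- 80% power on 3 df needs λ of about 10.90, so N ≈ 600 × 10.90/7.63 ≈ 857, about 860

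*Second scenario, equal increases*
- p̄ = 0.7575; Σ(pᵢ − p̄)² = 0.006075
- λ = 150 × 0.006075 / (0.7575 × 0.2425) = 4.96
- Power = 43.7% (simulation 43.1%), against 67% stated

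*Second scenario, 9 points as an average over the three arms.* Any variation between arms adds to λ. For +5/+9/+13 (69/74/78/82%), Σ(pᵢ − p̄)² = 0.009275, λ = 7.57 and power is about 63%. For +3/+12/+12 it is about 73%, and for +3/+9/+15 about 80%. So 44% is the lowest value under this reading.

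**Trying to reproduce the stated figures.** A one-sided 5% z test with unpooled variance, pooled telephone arms versus Control, comes close to both:
- Support arms (300) v Control (150): SE = √(0.69×0.31/150 + 0.80×0.20/300) = 0.04426; 0.11/0.04426 − 1.645 = 0.840; power 80.0%.
- All telephone arms (450) v Control (150): SE = √(0.69×0.31/150 + 0.78×0.22/450) = 0.04251; 0.09/0.04251 − 1.645 = 0.472; power 68.2%. Continuity-corrected and Fisher exact one-sided versions give 67.2% and 66.7%.

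The first of these omits the reminder-only arm and so uses 450 women, whereas the claim is made for 600.

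**Two-sided 5% versions of the 1-df contrasts.** Power = Φ[(difference − 1.96 × SE₀)/SE₁], with SE₀ from the pooled proportion and SE₁ unpooled.

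| Contrast | Proportions | SE₀ | SE₁ | Power |
|---|---|---|---|---|
| Support arms (300) v Control (150) | 80% v 69% | 0.04250 | 0.04426 | about 73% |
| Support arms (300) v Control + TEL (300) | 80% v 70.5% | 0.03524 | 0.03502 | about 77% |
| All telephone arms (450) v Control (150) | 78% v 69% | 0.04041 | 0.04251 | about 60% |

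**Sensitivity to the base rate.** With Control anywhere from 63% to 75% and the same increases, 3-df power runs from 57% to 73% in the first scenario and from 39% to 53% in the second with equal increases. Neither stated figure is reached in that range.

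**The case against.** The best defence is that the figures are not miscalculated but belong to a different test. One method, a one-sided 5% comparison of pooled arms with Control, gives close to 80% and 67% together, and the article says only "80% power (at the 5% level") without giving sidedness. That stands as a probable origin, and it rules out treating the numbers as a plain arithmetic slip. In particular, a reader might notice that referring the four-arm non-centrality of 7.63 to 1 df gives 78.9% and infer that the wrong degrees of freedom were used. The documents do not support that as the cause, since another route fits both figures better. Nor does the defence rescue the statement: no one-sided or pooled primary test is given, and the declared primary test is non-directional and keeps four arms.

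A second defence concerns the 67%. It is worded as telephone arms versus Control, which suggests a two-group contrast, and an increase spread across three arms need not be equal in each. This stands in part. On the two-group reading the shortfall is 7 points (60% v 67%), not 23. On the averaged reading, 67% lies inside the range that the 3-df test can give. So 44% is conditional on an equal increase and should not be quoted without that condition.

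Third, the title calls the trial a pilot, and feasibility comes first among the research questions. Nothing in the article says that a null result will be taken as proof of no benefit, so that consequence is a risk only. Even so, the article makes a formal power claim for a hypothesis test, and that claim should match the test.

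**Conclusion.** The point holds for the 80% figure: 80% is stated and about 63% is delivered by the planned four-arm chi-square, a shortfall of 17 points. This assumes 150 per arm, absolute increases of 0/3/11/11 points on a base of 69%, and the 5% level. Apart from reading the increases as absolute, these inputs are all fixed by the article.

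The 67% figure is a lesser, conditional finding. With exactly 9 points in each telephone arm, 67% is not reached on the 3-df test (about 44%) or on a two-sided pooled comparison (about 60%). The wording leaves room for unequal increases, under which 3-df power is higher.

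The defect is a mismatch between the power statement and the declared primary test. How the stated figures were obtained cannot be settled from the article.

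**What to change.** In Power calculations, state the test, its sidedness and the assumed increase in each arm for both claims. Then take one of two routes.

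1. Keep the four-arm chi-square as primary and restate its power at 600 women: about 63% for 69/72/80/80%, and about 44% for the second scenario if the increase is 9 points in every telephone arm.
2. Pre-specify a 1-df contrast as the primary test in Analysis and give its two-sided power: about 73% for support arms versus Control, about 77% for support arms versus Control plus TEL, or about 60% for all telephone arms versus Control at +9 points.

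Either route changes wording only. No extra enrolment is proposed. The cost is that the stated power becomes less favourable.

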## Methods/Design

We will adopt a simple, between-groups, four-arm prospective RCT design. The intervention will be targeted at those who are due to be sent a reminder letter i.e. non-attenders at a scheduled appointment. The four arms are: 1) Letter reminder (i.e. Treatment as usual: CONTROL); 2) Telephone reminder (TEL), 3) Telephone reminder plus telephone support (TEL-SUPP) and 4) Telephone reminder plus telephone support plus AR (TEL-SUPP-AR). The CONSORT diagram is shown in Figure 1.

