### Recruitment

Participants will be selected from those receiving an appointment for breast screening who do not telephone to cancel or re-arrange their appointment and who fail to attend their appointment before the reminder letter is due to be sent. Sampling will be from the lists of women for whom reminder letters are generated. We plan to target women from lower socio-economic areas, specifically women from Scottish Index of Multiple Deprivation (SIMD) vigintiles 1–12 (representing the lowest 60% of socio-economic areas in Scotland)^b^. The Scottish Index of Multiple Deprivation assesses deprivation levels for small geographical areas, based on income, employment, health, education, skills and training, housing, geographic access and crime. Based on the numbers of women who did not attend their designated appointment at the East of Scotland Breast Screening Service during 2012, we estimate that in 6 months we could recruit approximately 1,030 women. Currently the screening database does not include a telephone number for all women. We will therefore seek to obtain this information from other data collections (see Telephone numbers below). We would achieve our target for randomisation of 600 women, who are contactable by telephone, providing we are able to obtain approximately 58% of telephone numbers. We will seek to obtain telephone numbers before randomisation, so there is no bias in the Control group (for whom we do not require telephone numbers).

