### Primary and secondary outcomes

The primary outcomes, collected at 3-month follow-up, will be whether or not each patient makes another appointment for breast screening and whether or not they attended screening within 3 months of receiving their reminder (letter or telephone call). Previous attendances and previous failures to attend (attendance history) will also be collected at this time. Secondary measures for the two telephone support arms, collected during the telephone interview, are intention to make another appointment, anticipated regret, number of barriers to breast screening mentioned by participants, and specific barriers reported. In addition the percentage of participants for whom telephone numbers are obtainable at the outset is an important secondary outcome.

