## Endnotes

^a^For example, patients were sometimes concerned about potential long-term dependence or negative effects of taking their medication; reassuring them that the medication they were currently taking was not addictive, had been used extensively over many years, and had not been found to have serious side-effects over that time could help alleviate concerns and make patients less reluctant to take their medicine.

^b^At a national level for Scotland it is estimated that this split would represent current screening attendance rates of approximately 69% (vigintiles 1–12) versus 80% (vigintiles 13–20).

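### The 69% base rate in the power calculation is the general screening attendance in vigintiles 1–12, not a rate for the non-attenders who are randomised, so both power statements are unsupported for the trial population

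*Protocol article*

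**What the plan says.** All references are to the protocol article.

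- **Power calculations.** For 600 women and a 5% significance level, the section claims 80% power if attendance rises by 11 points in each of the two support arms and by 3 points in TEL, with Control unchanged. The starting point is given as "assuming a base attendance rate of around 69% (as currently present in vigintiles 1–12". A second claim is 67% power for a 9% increase across the three telephone arms against Control.
- **Endnote b.** At national level, "this split would represent current screening attendance rates of approximately 69% (vigintiles 1–12) versus 80% (vigintiles 13–20".
- **Methods/Design.** "The intervention will be targeted at those who are due to be sent a reminder letter i.e. non-attenders at a scheduled appointment".
- **Recruitment.** Participants are those who neither cancel nor rearrange and who "fail to attend their appointment before the reminder letter is due to be sent". Inclusion criteria, Design, and Sampling and randomisation repeat this and add that a telephone number must be obtainable.
- **Primary and secondary outcomes.** The attendance outcome is "whether or not they attended screening within 3 months of receiving their reminder (letter or telephone call".
- **Analysis.** The primary test is a chi-square across the four arms, with all women analysed as allocated. Allocation is 1:1:1:1, so 150 per arm.

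**The concern.** The base rate and the randomised women come from different populations. The Abstract and the Screening uptake section use attendance to mean the share of invited women who attend, and endnote b's 69% reads the same way. Every woman in the trial has been selected for having missed an appointment. Her chance of attending in the next three months is a conditional rate, and nothing in the document estimates it.

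Both power statements start from this rate. The meaning of the target also depends on it: 11 points on 69% is a relative rise of 11/69 = 16%, while 11 points on 20% is 11/20 = 55%. If the base rate is not for these women, a reader cannot tell whether 600 is enough or whether an 11-point increase is a realistic aim.

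**Working it through.** **1. The protocol's own figure.** Inputs: 69%, 72%, 80%, 80%; 150 per arm; 4×2 Pearson chi-square, 3 df, 5% level, critical value 7.815.

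Noncentrality is λ = 150 × Σ(pᵢ − p̄)² / [p̄(1 − p̄)]. Here p̄ = 0.7525 and the deviations are −0.0625, −0.0325, +0.0475, +0.0475, so Σ = 0.009475 and λ = 1.42125 / (0.7525 × 0.2475) = 7.63. Power is **63%**, confirmed by simulation, against the stated 80%. That shortfall exists before the base rate is questioned. It makes 63% the fair comparator for step 3.

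**2. What 69% implies for the randomised women.** Let f be the share of invited women who attend first time, c the share who decline and never attend (and so are not randomised), and r the attendance after the reminder among the rest. If 69% is final attendance:

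0.69 = f + (1 − f − c) r, so r = (0.69 − f) / (1 − f − c).

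The documents give neither f nor c, so these values are assumptions:

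| f | c | r |
|---|---|---|
| 50% | 0 | 0.19/0.50 = 38% |
| 60% | 0 | 0.09/0.40 = 22.5% |
| 65% | 0 | 0.04/0.35 = 11% |
| 60% | 10% | 0.09/0.30 = 30% |
| 50% | 15% | 0.19/0.35 = 54% |

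Setting r = 0.69 gives 0.31f = 0.69c, or c ≈ 0.45f. If instead 69% is attendance before any reminder, it carries no information about r.

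**3. Power of the planned test at other Control rates.** With the absolute increases 0/3/11/11 kept, Σ does not change and λ = 1.42125 / [p̄(1 − p̄)], where p̄ = Control rate + 0.0625:

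| Control rate | λ | Power, 3 df, N = 600 |
|---|---|---|
| 10% | 10.44 | 78% |
| 15% | 8.49 | 68% |
| 20% | 7.34 | 61% |
| 30% | 6.15 | 53% |
| 40% | 5.72 | 50% |
| 69% (protocol) | 7.63 | 63% |

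With the planned odds ratios kept instead (0.72/0.28 ÷ 0.69/0.31 = 1.16 for TEL; 0.80/0.20 ÷ 0.69/0.31 = 1.80 for the support arms), power is 41%, 63%, 73% and 77% at Control rates of 10%, 20%, 30% and 40%.

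**4. The 11-point target.** Endnote b's two rates differ by 80 − 69 = 11 points, and the Discussion speaks of reaching about 80%. If that gap is the source of the target, it is a gap between populations of invited women. Among reminder-list women an 11-point gain adds 0.11 × (1 − f) to overall uptake, which is 5.5 points at f = 50% and about 4 points at f = 65% (c = 0).

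**The case against.** Four objections deserve weight.

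**A reader might infer that 69% is impossible for these women.** The formula does not show that. Women who telephone to decline are not randomised, and removing them raises r. At c ≈ 0.45f it reaches 69% with f above zero (for example f = 50%, c = 22.5%). That needs an implausibly large declining group, but it is not excluded by arithmetic. Requiring a telephone number may also shift the rate. What stands is narrower: 69% was not derived for this group, and the document gives no reason to expect it there.

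**A reader might infer that the wrong base rate makes the trial underpowered.** The documents do not support a direction. Against 63% at the protocol's own inputs, power with the same absolute increases is higher at Control rates of 10–15% and lower at 20–40%. The drop from 80% to 63% is a different fault and should not be charged to the base rate.

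**A reader might take it as fact that the 11 points are the deprivation gap.** The protocol gives no source for them. The match with endnote b is suggestive, but the Theoretical background section also cites gains of similar size: 8 points in a telephone coaching study and 10% in a medication study.

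**The trial is a pilot.** Feasibility and acceptability come first among its research questions, and a wrong planning rate does not bias the randomised comparison. Both statements are correct. The protocol nevertheless makes a formal power claim and ties a significant result to advice on implementation, so the claim should describe the women studied.

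**Conclusion.** The concern holds in this form: the 69% is general attendance in vigintiles 1–12, the randomised women are non-attenders on the reminder list, and both power statements are therefore unsupported for the trial population. This follows from the document's own text. It is not a detail left to a fuller protocol or analysis plan, because the article states both the rate and the eligible population.

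No single corrected power exists, because the Control rate is not in the documents. Over assumed Control rates of 10–40%, the planned 3-df test at 600 women has 50–78% power with the absolute increases kept and 41–77% with the odds ratios kept. None of the values reaches 80%, but neither does the 63% at the protocol's own rate. The implied Control rates of 11–54% rest on assumed f and c and on reading 69% as final attendance. The link between the 11 points and endnote b is an inference.

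**What to change.** In Power calculations:

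1. Replace 69% with the observed attendance within 3 months of the reminder letter among vigintile 1–12 women on the East of Scotland service's 2012 reminder lists. The Recruitment section already draws on that year's non-attender records for its estimate of 1,030 women.
2. Justify the target increase as an as-allocated increase in that group, so that it allows for women who cannot be reached or who decline the call. State where the figure comes from.
3. Restate the power of the planned 3-df test at 600 women over a range of Control rates, for example 10–40%, and revise the second power statement on the same base.

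The cost is one query of data the service holds and revised wording. The sample size stays at 600, and the sponsor should expect that the restated power may be less favourable than 80%.
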